### 2.11. Statistical Considerations and Methods

#### 2.11.1. Sample Size

The planning aims to obtain data on hemodynamic parameters and differences in hemodynamics in the clinical course of 20 patients.

### 2.12. Study Inclusion and Patient Treatment

Patients with cardiogenic shock are screened and transferred to the cardiac catheterization laboratory as soon as possible after admission or after being transferred from another hospital. After checking the inclusion/exclusion criteria and receiving consent, the patient will be included in the study. Left heart and right heart catheter examinations are performed and the coronary vessel responsible for the infarct is recanalized using percutaneous coronary intervention (PCI) as soon as possible. In case of an indication for immediate bypass surgery, the study is not discontinued, but further evaluation according to the intention-to-treat principle will apply. Further medicinal measures for the treatment of acute myocardial infarction, circulatory-support therapy with catecholamines, assisted or volume-controlled ventilation, etc., are carried out according to the decision of the physician in charge according to recognized therapy guidelines.

#### 2.12.1. Documentation of Hemodynamic Parameters

Hemodynamic parameters such as arterial systolic and diastolic blood pressure, mean blood pressure and heart rate are documented in the cardiac catheterization laboratory prior to the implantation of Impella CP^®^. Pulmonary artery catheter examination will measure the various pressures (e.g., diastolic, systolic and mean pulmonary artery pressure (PAP), pulmonary capillary wedge pressure (PCWP)) and resistances (e.g., systemic and pulmonary vascular resistance). This is repeated at defined intervals together with an arterial and mixed venous blood gas analysis for determination of pH, serum lactate and standard base excess.

#### 2.12.2. Echocardiography

Echocardiography is performed before and after Impella CP^®^ implantation as well as on a daily basis until the Impella CP^®^ is explanted. Parameters of the left and right ventricular size and function as well as the documentation of possible valve abnormalities are standard and will be stored within the internal Picture Archiving and Communication System (PACS). Parameters are listed in Table 2.

#### 2.12.3. Additional Documentation of Hemodynamic Parameters

At the end of the examination in the catheterization laboratory, the hemodynamic parameters from pulmonary artery catheterization are documented again about 30 min after implantation of the Impella CP^®^. Furthermore, a new arterial and mixed venous blood gas analysis is performed with additional determination of pH, serum lactate and standard base excess. Echocardiographic parameters are recorded according to the protocol.

#### 2.12.4. Post-Implantation

The patients are monitored until they are transferred to the intensive care unit. The flow of the device should be optimized according to clinical goals (MAP ≥ 65 mmHg).

#### 2.12.5. Supportive Therapy in the Intensive Care Unit

Further intensive medical therapy is carried out according to generally recognized guidelines. Systemic anticoagulation with unfractionated heparin will be used for the duration of left ventricular support (target activated clotting time around 180 s).

Drug therapy with catecholamines (noradrenaline, dobutamine, possibly suprarenin, vasopressin) according to current recommendations is possible. The use of calcium sensitizers (e.g., levosimendan) or other hemodynamically relevant drugs (e.g., PDE inhibitors) are also possible according to an individual intensive care medicine assessment [14]. The aim, independent of the study, is to achieve a mean arterial blood pressure of at least 65 mmHg. All patients receive an invasive hemodynamic measurement using a standard pulmonary artery catheter. The daily doses of catecholamines and other hemodynamic drugs are documented. Furthermore, the daily fluid balance/management up to the explanation are recorded. If the use of a renal replacement therapy is necessary, the duration and type of the procedure are documented. In addition, the duration of any mechanical ventilation, the time of extubation and any reintubation that may be necessary are documented. Left ventricular ejection fraction is determined again within 24 h and after 7 days.

As part of the recording of the intensive medical treatment, the SAPS (Simplified acute physiology score) II score is recorded serially every day in the intensive care unit. To determine inflammatory parameters, as well as liver and kidney functions, a full blood work-up is recorded daily including C-reactive protein (CRP) and procalcitonin (PCT). All other laboratory parameters are determined at least once a day according to the documentation sheets in the routine laboratory program. Ethylenediaminetetraacetic acid (EDTA), blood, serum and plasma are stored at all times (before, after implantation, day 1–3 and 7) for later molecular biological analysis.

#### 2.12.6. Hemodynamic Monitoring in the Intensive Care Unit

At least three times a day the measuring of selected hemodynamic parameters takes place and includes: arterial systolic/diastolic blood pressure, mean arterial pressure, heart, arterial blood gas analysis with additional determination of pH, base excess, serum lactate and parameters from invasive monitoring via PAC (pulmonary capillary wedge pressure (PCPW), pulmonary artery pressure (PAP), cardiac output (CO), central venous pressure (CVP), mixed venous oxygen saturation (mvO_2_Sat), pulmonary vascular resistance (PVR), and systemic vascular resistance (SVR)).

#### 2.12.7. Weaning and Explantation of the Impella CP^®^ Device

The duration of therapy is determined by the need for supportive therapy with catecholamines. In previous studies, the mean duration of mechanical circulatory support was 3–4 days [21]. The main criterion for starting weaning from mechanical circulatory support is sustained hemodynamic stability (systolic RR > 90 mmHg for >60 min) without therapy with catecholamines and without signs of peripheral end-organ hypoperfusion. Impella^®^ flow is reduced in steps every 3 h; after 3 h at level 2, another echocardiography, hemodynamic measurement and blood sampling followed by explanation of the Impella^®^ take place. Standardized femoral artery access site closure takes place after explantation via a suture mediated percutaneous system as a first option (Perclose ProGlide^®^, Abbott laboratories, Abbott Park, Chicago, IL, USA)

#### 2.12.8. 30 Day Follow-Up

A new echocardiographic assessment is carried out before discharge from the hospital. After 30 days, the patient’s vital status is again ascertained through contact. All clinical events are verified by obtaining the original documentation. In addition, dyspnea according to the New York Heart Association (NYHA)-classification, angina pectoris according to the Canadian Cardiovascular Society (CCS)-classification and quality of life according to the EuroQol (EQ)-5D questionnaire are recorded.

#### 2.12.9. Follow-Up Plan

Further treatment of the patients after the end of the clinical trial is carried out by the general practitioners/resident and/or cardiologists. In the event of undesirable side effects, patients are instructed to contact the study director or one of his representatives in accordance with Section 7, Paragraph 2, Item 13 of the Good Clinical Practice (GCP)-ordinance.

### 2.13. Methods against Bias

#### 2.13.1. Blinding and Treatment Bias

Blinding is not possible because of the intervention used. Methods used against bias are standardized examination protocols to even out systematic differences due to differing expertise at all levels, and an independent clinical endpoint committee to evaluate adverse events other than death; high clinical standards are maintained with regard to the number of PCIs performed/year (about 1000) of patients treated in cardiogenic shock and participation in clinical studies. Furthermore, our study center has a certified, cardiac ICU specialized in the treatment of cardiac shock and application of Impella CP^®^ that are embedded in a quality management system. Investigators are trained in good clinical practice (GCP). All medical professionals involved are qualified and hold the appropriate national diploma or at least operate under surveillance of a senior staff member.

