## 2. Methods and Analysis

### 2.1. Study Design

JenaMACS (Jena Mechanical Assist Circulatory Support) is a monocenter, prospective, open-labeled, proof-of-concept register study. JenaMACS will assess the impact of the Impella CP^®^ assist device on acute and subacute hemodynamic effects after implantation in patients with cardiogenic shock in addition to standard medical therapy. Figure 1 shows the study flow.

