### 2.6. Objectives

#### 2.6.1. Primary Objective

The primary objective of the JenaMACS register is to investigate the potential benefit of the Impella CP^®^ on hemodynamics and left ventricular unloading in patients with cardiogenic shock after 24 h by using a ramp test protocol (Table 2 and Figure 1). The ramp test is performed as follows: During a step by step reduction of the Impella^®^ flow support (ramp test), hemodynamic (PCWP, SV) and echocardiographic parameters (left ventricular ejection fraction (LVEF), left ventricular end-diastolic diameter (LVEDD), and grading of mitral valve regurgitation) are recorded at each level from highest (P8) to lowest (P2). Measurements take place 10 min after adjusting the console to each flow level. In theory, mechanical assistance for unloading of the left ventricle might lead to a faster decrease in LVEDD, PCWP and mitral regurgitation and faster increase in LVEF and SV that could be translated into improved left ventricular recovery

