### 2.7. Endpoints

The primary endpoint of the JenaMACS register study is the change in hemodynamic and echocardiographic parameters after 24 h during the ramp test at different Impella^®^ support levels. Parameters to be measured are listed in Table 2 and a scheme is provided in Figure 2. Secondary endpoints are listed in Table 4.

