#### 2.9.3. Transthoracic Echocardiography

Transthoracic echocardiography (TTE) is performed using the ultrasound system Vivid S70^®^ (GE^®^, Boston, MA, USA) and the recordings are processed via dedicated software (Image-Arena ™ Version 4.6; TomTec Imaging Systems, Unterschleissheim, Germany). Echocardiographic evaluation is carried out in a standardized comprehensive fashion and encompasses acquisition of features of left/right ventricular and valvular function (Table 2).

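### The stated reason for no blinding covers treatment but not the reading of ramp-test echo recordings, and no listed safeguard covers reader expectation in those primary measures

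*Protocol article*

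**What the plan says.** All references are to the protocol article.

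- **Design (2.1).** The study is a "monocenter, prospective, open-labeled, proof-of-concept register study".
- **Primary endpoint (2.7).** It is "the change in hemodynamic and echocardiographic parameters after 24 h during the ramp test at different Impella^®^ support levels".
- **Ramp test (2.6.1 and Table 2).** Support is lowered stepwise through P8, P6, P4 and P2. Section 2.6.1 names PCWP and SV as the hemodynamic parameters, and LVEF, LVEDD and mitral regurgitation grade as the echo parameters. "Measurements take place 10 min after adjusting the console to each flow level". The same section says that unloading should lower LVEDD, PCWP and mitral regurgitation and raise LVEF and SV.
- **Echo handling (2.9.3 and 2.12.2).** Transthoracic echo is done on a named ultrasound system, and "the recordings are processed via dedicated software"; this section points to Table 2, the ramp-test table. Section 2.12.2 adds that echo findings are kept in the hospital's picture archive.
- **Blinding (2.13.1).** "Blinding is not possible because of the intervention used". The measures listed against bias are standardized examination protocols, "an independent clinical endpoint committee to evaluate adverse events other than death", and the experience, certification and training of the centre and its staff.
- **Measurement bias (2.13.2).** The measures are documentation in case report forms, follow-up of all patients, and on-site and central monitoring.

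**The concern.** The blinding sentence gives one reason, the nature of the intervention, and draws an unqualified conclusion. The reason settles that patients and treating staff know the device is in place and at what setting. It does not settle whether the person who later measures a recorded loop must know that setting.

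The distinction matters because the primary contrast is between support levels within the same patient. LVEDD and LVEF need a reader's tracing or judgement, and mitral regurgitation is an ordinal grade. If the reader knows which loop is P8 and which is P2, and also knows the expected direction, any tendency to read towards expectation tracks the support level. It then adds directly to the estimated change. Averaging over patients does not cancel such a shift, and monitoring of case report forms would not detect it.

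**Working it through.** **1. Does the stated reason reach the echo reading?** Set the sections side by side:

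| Step | Known to depend on the visible intervention? | Source |
|---|---|---|
| Setting the console, P8 to P2 | Yes | 2.6.1, Table 2 |
| Acquiring images and catheter values at the bedside | Yes | 2.6.1 |
| Measuring recorded echo loops in separate software | Nothing in the document says so | 2.9.3, 2.12.2 |

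The third step can be separated from the first two if the ramp loops are stored. Storage is an inference. Section 2.12.2 describes echo before and after implantation and daily, and does not name each ramp level. The inference is reasonable because 2.9.3 says echo recordings are processed in software, and both sections refer to Table 2.

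**2. Does another safeguard cover it?** The endpoint committee covers adverse events only. Standardized examinations are said to even out differences in expertise, which is not the same as expectation. Case report forms, follow-up and monitoring check documentation. None masks the reading.

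**3. How much of the endpoint is concerned?** Of the three echo and two catheter parameters named in 2.6.1, masked reading reaches the three echo ones. Of the 13 columns recorded per level in Table 2, it reaches five: MR, LVEDD, LVESD, LVEF and RVEDD.

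**4. What could a reading shift do?** The plan has no figure to reproduce: section 2.11.1 gives 20 patients without an effect size, SD or power. The following is an illustration.

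- From the document: n = 20 (2.11.1); significance level 5% (2.11.2).
- Assumed: two-sided paired t test of P8 against P2, all 20 pairs complete, true change zero, and a shift from unmasked reading of *b* SDs of the paired difference.
- Formula: the test statistic follows a non-central t distribution with n − 1 = 19 degrees of freedom and non-centrality λ = b × √20. The false-positive rate is P(|T| > 2.093).

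| Assumed shift b (SD of paired difference) | λ = b × 4.472 | False-positive rate |
|---|---|---|
| 0 | 0 | 5.0% |
| 0.1 | 0.447 | 7.1% |
| 0.2 | 0.894 | 13.6% |
| 0.25 | 1.118 | 18.6% |
| 0.3 | 1.342 | 24.7% |
| 0.5 | 2.236 | 56.5% |

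**5. Size of the remedy.** 4 support levels × 20 patients = 80 clip sets.

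**The case against.** **The sentence may be meant only for treatment.** It stands under a heading on blinding and treatment bias, and measurement bias has its own section. This is a fair reading of the intent. But 2.13.2, where masked reading would belong, offers nothing in its place, so the reader is left with an unqualified statement and no safeguard.

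**An article leaves imaging detail to the full protocol.** This stands in part. Clip labels and reading order are such details, and the article does not say who reads the echoes, how many readers there are, or whether ramp values are taken live or offline. So one cannot say that the plan has loops read with the level known, only that it does not prevent this. The blinding statement itself is not an omitted detail: it is made in the text, and its reason does not support its full scope.

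**A reader might infer that masked reading would remove observer bias from the primary endpoint.** The documents do not support that. Staff who know the setting still acquire the images, PCWP and SV are untouched, and the image itself may hint at the support level (an assumption; the document is silent). Nor does masking deal with the fixed descending order from P8 to P2, which is a separate matter.

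**A reader might also infer that one existing reader could do this at no staff cost, or that the missing control group is what makes the bias harmful.** No reader is named, so the first is an assumption. The second adds little: the contrast is within patient, and a reader who knows the level would distort it with or without a control arm.

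**The false-positive rates are weakly anchored.** This stands. The shifts are assumed, a t test does not suit an ordinal grade, and section 2.11.2 names analysis of variance, independent-samples tests and regression, but no paired test. With fewer complete pairs, the inflation at a given shift would be smaller.

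**Conclusion.** The point holds in a limited form. The reason in 2.13.1 justifies open treatment, not unmasked reading of the recorded echo loops, and neither bias section protects LVEDD, LVEF or mitral regurgitation grade from reader expectation. Masking would reduce that bias, and only in the echo components.

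The conclusion assumes that ramp-test loops are, or can be, stored and measured away from the bedside. The document makes this likely but does not state it for each level. The size of the actual bias is unknown. The illustrated rates, from 7.1% at 0.1 SD to 56.5% at 0.5 SD, show how sensitive a 20-patient within-patient comparison could be; they do not estimate the error rate of this study. The change is worth making because it is cheap and concerns primary measures. It is no ground for calling the design invalid.

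**What to change.** Replace the blanket statement in 2.13.1 with one that says treatment cannot be blinded but echo reading can be masked in part. Then add to 2.13.2 that:

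- ramp-test echo recordings are stored or exported without the support level and given random codes;
- whoever already reads the study echoes measures them offline in random order;
- the key linking code to P level is kept apart and merged only after the echo values are locked;
- bedside image acquisition and the catheter measures, including PCWP and SV, remain unmasked, and this is reported as a limitation.

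The cost is coding and reordering about 80 clip sets and a short delay before the study values are available. Sample size, device, ramp schedule and patient care do not change. If ramp values are at present taken only live, the offline measurement is additional reading time, which the document does not allow one to estimate.

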### 2.10. Safety, Possible Complications and/or Risks

Study participation is not associated with any additional risks for patient’s safety. The Impella CP^®^ is a CE-approved medical device and part of routine, clinical use for cardiogenic shock and other indications. The use of a Swan-Ganz Catheter is standard practice in cardiogenic shock patients. For safety assessments, documentation of relevant events regarding Impella CP^®^ treatment include the aspects listed in Table 5.

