#### 2.13.2. Measurement Bias

At each visit, the measured parameters are documented in the case report forms (CRFs). In addition, all patients will be followed-up after screening and implantation of the Impella CP^®^ system. Finally, monitoring (on-site and central) will be carried out during the trial by staff of the Department of Cardiology and of the Center for Clinical Studies, Jena University Hospital.

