BGA including lactate	X	X	X	X	X	X				
Creatinine clearance **	X		X	X	X					
Blood Samples (Measurement of biomarkers)	X	X	X	X	X	X	X	X	X	X
PAC—Hemodynamics	X	X	X	X	X	X				
Measurement of parameters of hemodynamics ^∆^	X	X	X	X	X	X				
TTE	X	X	X	X	X	X	X	X		
Dose of isotopes and vasopressors	X	X	X	X	X	X	X	X		
Impella CP^®^ data	X	X	X	X	X	X				
SAPS-II Score		X	X	X	X	X				
CCS category								X	X	X
NYHA category								X	X	X
Quality of Life (EQ-5D)							X	X	X	X
Measurement of the neurological outcome (GCS) ^∆^	X	X	X	X	X	X	X	X	X	X

^∆^ Data documentation from clinical routine (if available), * every day until hemodynamic stabilization; ** Clearance calculated according to Cockcroft-Gault formula; ^+^ after Impella explantation; SAPS = Simplified Acute Physiology Score; ECG = Electrocardiography; TTE = Transthoracic echocardiogram; PAC = Pulmonary artery catheterization; NYHA = New York Heart Association; CCS = Canadian Cardiovascular Society; GCS = Glasgow coma scale; PCI = Percutaneous, coronary intervention; BGA = Blood gas analyses. EQ—5D = EuroQol questionnaire.

**Table 4 jcm-11-04623-t004:** Secondary endpoints of the JenaMACS study.

Secondary Endpoints
- Change of hemodynamic and echocardiographic parameters after 10 min, 30 min and every 8 h of Impella support - Need, type, dose and duration of inotropic/vasopressor treatment. - Time until hemodynamic stabilization (lactate < 2 mmol/L; mean arterial pressure > 65 mmHg) after implantation. - Change in inflammatory parameters over time. - Mean and area under the curve of serum-lactate measured every 8 h for 48 h after implantation. - Mortality defined as mortality rate in the hospital or anywhere after discharge, within 12 months after implantation. - Changes in kidney function after implantation. - Need and duration of renal replacement therapy (CVVHD) and mechanical ventilation after implantation. - Length of stay at ICU after implantation. - Need for an active assist device or heart transplantation after implantation. - SAPS II Score at baseline and every 24 h during Impella CP^®^ support. - EQ-5D-questionnaire including EQ VAS after implantation. - Neurological outcome (GCS) after implantation. - Safety aspects such as major bleeding according to GUSTO/BARC definition, critical limb ischemia, sepsis, hemorrhagic or ischemic stroke

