CVVHD = continuous veno-venous hemodialysis, ICU = intensive care unit, SPAS = Simplified acute physiology score, EQ—5D = EuroQol questionnaire, VAS = Visual analogue scale, GCS = Glasgow Coma Scale BARC = Bleeding academic research consortium, GUSTO = Global use of streptokinase and t-PA for occluded coronary arteries, PCT = procalcitonin.

**Table 5 jcm-11-04623-t005:** Safety of the JenaMACS trial. Any of the mentioned adverse events (AE) is considered as a serious adverse event (SAE) if it is directly caused, may have caused in the past or may cause in the future death or a serious aggravation of the state of health of a patient, user or another person if the incident was caused by the medical device. The events will be recorded from the moment the medical device is unpacked and inserted into the patient until follow-up at discharge.

Safety of the Trial
- Peri-procedural complications within 7 days combined from: pericardial effusion, stroke, major bleeding, embolization, intracranial bleeding. - Device related: thrombus, breakage, malfunction, allergic reactions. - Vascular access related complications requiring intervention/surgery. - Procedure related death. - Post-procedure infection rate. - Sepsis with clinical signs of infection and increased PCT (>2 pg/mL). - Peri-procedural outcomes at 7 and 30 days after implantation. - Bleeding requiring transfusion (BARC 2—5). - Severe and moderate bleeding complications (GUSTO definition). - Stroke. - Severe limb ischemia/peripheral vascular complications.

BARC = Bleeding academic research consortium, GUSTO = Global use of streptokinase and t-PA for occluded coronary arteries, PCT = procalcitonin.

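### The independent endpoint committee's remit leaves out all deaths, so the one safety item that attributes a death to a cause has no independent review

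*Protocol article*

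**What the plan says.** Section 2.13.1 of the protocol article states that "Blinding is not possible because of the intervention used" and lists methods against bias. One of them is "an independent clinical endpoint committee to evaluate adverse events other than death". The exclusion is explicit and covers every death.

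Section 2.10 gives Table 5 its standing: "For safety assessments, documentation of relevant events regarding Impella CP^®^ treatment include the aspects listed in Table 5". Table 5 includes "Procedure related death". Its caption classes a listed event as serious on a test of causation, with death among the outcomes: "if the incident was caused by the medical device". Section 2.11.2 says that all observed safety events will be tabulated with 95% confidence intervals.

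Table 4 defines the mortality endpoint without reference to cause: "Mortality defined as mortality rate in the hospital or anywhere after discharge, within 12 months after implantation".

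Two further controls bear on this. Section 2.12.8 says of follow-up that "All clinical events are verified by obtaining the original documentation". Section 2.13.2 says that "monitoring (on-site and central) will be carried out during the trial by staff of the Department of Cardiology", together with the hospital's own centre for clinical studies.

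**The concern.** An endpoint committee is most useful where an outcome depends on judgement and the people closest to the patient know the treatment. Whether a patient has died needs no judgement. Whether the procedure caused the death does, particularly in cardiogenic shock, where the article itself cites a high background mortality. The committee's remit draws no line between these two questions. It drops death altogether, so non-fatal complications are reviewed independently and the cause-of-death label is not.

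At stake is the credibility of one reported safety figure. With no comparison group, the study cannot subtract the deaths expected from shock alone, so nothing in the data would expose a misattribution.

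**Working it through.** **Step 1. Compare each item with the committee's remit.**

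| Item | Where | Needs a judgement of cause? | In the remit of 2.13.1? |
|---|---|---|---|
| All-cause mortality to 12 months | Table 4 | No | No, and no harm follows |
| Non-fatal complications (bleeding, stroke, limb ischemia, device and access-site events) | Table 5 | Some do | Yes |
| Procedure-related death | Table 5 | Yes | No |
| Device causation of a death, for the seriousness test | Table 5 caption | Yes | No, because death is excluded |

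The gap is confined to the last two rows.

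**Step 2. Look for another independent view of cause.** Checking original documents (2.12.8) confirms that an event took place; it does not assign a cause. Monitoring (2.13.2) is done in-house. The article names no one as assessor of cause of death.

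**Step 3. Scale, as an illustration only.** The plan states no figure for procedure-related death, so there is none to reproduce.

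Inputs: n = 20 (Section 2.11.1); background mortality 30–70% (Section 1, no time horizon given).

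- Upper illustration of deaths to review: 20 × 0.30 = 6 and 20 × 0.70 = 14.
- Effect of reclassifying one death: 1/20 = 5 percentage points.
- Exact (Clopper-Pearson) 95% limits for x deaths in n: lower = Beta quantile at 0.025 with parameters (x, n − x + 1); upper = Beta quantile at 0.975 with parameters (x + 1, n − x). For x = 0 the lower limit is 0 and the upper limit reduces to 1 − 0.025^(1/20) = 16.8%.

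The number of procedure-related deaths is not given. Assuming 0 to 4:

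| Deaths attributed | Rate | Exact 95% CI |
|---|---|---|
| 0/20 | 0% | 0 to 16.8% |
| 1/20 | 5% | 0.1 to 24.9% |
| 2/20 | 10% | 1.2 to 31.7% |
| 3/20 | 15% | 3.2 to 37.9% |
| 4/20 | 20% | 5.7 to 43.7% |

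**Step 4. Limit on the range of 6 to 14.** The Table 5 caption records events from unpacking of the device until follow-up at discharge, although the table also lists outcomes at 30 days. Deaths after the recording window would not need classification, so 6 to 14 is a ceiling under the cited mortality.

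**The case against.** The strongest reply is that this is a condensed article, and that the committee's charter and the procedure for judging causality commonly sit in the full protocol. That protects what the article leaves out. Here the article states the remit and states the exclusion, so a charter that had the committee judge procedure-related death would conflict with 2.13.1.

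Second, the committee is not shut out of fatal cases. A stroke, a major bleed or a device malfunction is an adverse event whether or not the patient later dies, and on a plain reading it stays in the remit. This stands and narrows the point: the complication can be reviewed independently, and only the step from complication to cause of death is not.

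Third, the item is one descriptive entry in Table 5. It is not among the Table 4 secondary endpoints, and with 20 patients its rate is imprecise whoever decides; the intervals for 0/20 and 2/20 overlap widely. This also stands and keeps the point small.

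A reader might infer that unblinded treating staff decide which deaths count against the device, and that the rate will therefore be too low. The documents support neither. No section names the assessor, so site attribution is a likely default and not a stated fact. Nothing shows the direction of error: a shock death may be put down to the procedure as well as the reverse. Nor does the limited remit contradict the aim of Section 2.13; it leaves that safeguard incomplete.

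**Conclusion.** The point holds in a limited form. The remit in 2.13.1 and the content of Table 5 do not fit together: the one cause-specific death item lacks the independent review given to the other adverse events, and no substitute is named. The primary endpoint and all-cause mortality are untouched, and no sample size or analysis changes.

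The numerical size rests on two assumptions: that the cited 30–70% mortality applies to these patients, and that all such deaths fall inside the recording window. The second probably overstates the count. What does not depend on them is the 5-point shift per reclassified death in 20 patients. This is a cheap improvement to a safety figure, not a threat to the study's main result.

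**What to change.** Amend Section 2.13.1 so that the committee reviews the non-fatal adverse events as now and, in addition, judges for each death within the Table 5 recording window whether it was related to the procedure and whether it was related to the device. Leave all-cause mortality unadjudicated, and report it beside procedure-related death so that readers see both counts. While making the change, say which date closes the recording window for deaths, since Table 5 mentions both discharge and 30 days.

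The cost is a small number of further case reviews for a committee that the plan already provides: at most about 6 to 14, and fewer if only deaths up to discharge count. The reviews can be done from source documents, including for patients already enrolled, and they alter nothing in patient care.
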